#### Intervention description {11a}

After completing the baseline outcome measures, participants will be randomly assigned to either the intervention arm (HQ-SC plus g-IPT) or the control arm (HQ-SC). All trial participants will receive HQ-SC. Those assigned to the intervention arm will subsequently receive g-IPT.

*High-quality standard care*: In both Kenya and Lebanon, high-quality standard care (HQ-SC), known as “Doing What Matters in Times of Stress” [38], teaches participants how to use a stress management guide over the course of two group sessions, with each taking between 60 and 90 min. This guide aids them in developing practical skills to handle stress effectively. Grounded in Acceptance and Commitment Therapy (ACT) [39], it is designed for anyone over 18 years of age, with its brief nature allowing for quick reading. This intervention will be extended to all women in the trial, regardless of other available interventions in the pathway of standard care.

*Group interpersonal psychotherapy* (g-IPT): g-IPT is an evidence-backed, time-limited psychotherapy tailored for depressive disorders, encompassing post-natal depression. It has been practised and validated in LMICs by professionals and trained laypersons [40]. The therapy’s goal is to address interpersonal triggers of depressive episodes, segmented into four problem areas: grief, disputes, life changes, and loneliness/social isolation [41]. The World Health Organization (WHO) has globally disseminated group IPT through a nine-session protocol (1 individual and 8 group sessions), which is employed in this study [22]. These g-IPT sessions typically last 1.5 h, except for the initial individual session (up to 2 h) and the concluding session (2–3 h). These sessions are held weekly and consist of groups of 6–10 women.

*Adaptation of g-IPT*: IPT had been previously adapted to the Kenyan and Lebanese contexts for cultural and situational relevance in earlier studies [42–44]. However, further refinements have been made for this specific study population and regional contexts. These adaptations in content and delivery of g-IPT contemplate each location’s cultural norms for young mothers related to intimacy, authority, daily routines, interactions, child-rearing practices, and communication standards (like expressions of closeness, including mother–child attachment, aggression, assertiveness, etc.). Also considered are the current societal, familial, and individual stressors arising from social instability, increased poverty, and scarce resources, which are prevalent in both regions, albeit in varied forms. Notably, issues like domestic violence and grave livelihood challenges are anticipated to be pertinent for both nations. These adaptations were meticulously documented during the pre-trial and feasibility stages, employing the Framework for Modification and Adaptations-Enhanced [45]. Feedback from participants in the feasibility trial was integrated iteratively, refining the g-IPT model, which culminated in the final clinical protocol to be assessed in the RCT.

*g-IPT training*: For the sake of sustainability and scalability, the qualifications of g-IPT providers will differ between the two study sites. In Lebanon, in line with recent national regulations for accredited psychotherapy provision, trial providers will be licensed psychologists associated with primary care locations, with one facilitator per group. In contrast, Kenya, which has adopted a task-shifting approach to bolster capacity in primary care [46], will utilise community health workers, assigning two facilitators per group. Supervisors across both sites will be professionals previously trained in IPT, such as psychologists, psychiatrists, and social workers. The training and implementation of the intervention will be overseen by two US-based g-IPT master trainers.

We will adopt the apprenticeship model of psychotherapy training, which entails a three-tiered system for sustainable capacity building: master trainers, local supervisors, and g-IPT providers [47, 48]. The master trainers, aided by local supervisors, will conduct a 4-day didactic g-IPT workshop for facilitators. This will be followed by a standardised g-IPT knowledge test with a set “pass” threshold. Facilitators who pass this test will subsequently receive supervision in weekly meetings (either onsite or online) for two groups per facilitator. These sessions will be led by the local supervisors, with occasional assistance from the master trainers. Facilitators’ competence will be gauged using a g-IPT fidelity checklist during these supervision sessions. Only facilitators who achieve a mean score per group that meets or exceeds 75% of the “adequately competent” benchmark at designated intervals (one during the pre-group phase, one at the outset, two mid-way, and one at the end) will be certified to conduct the study. Following the completion of their inaugural training case, trainees will attend a 2-day advanced workshop. Orchestrated by master trainers and local supervisors, this workshop will fortify both knowledge and expertise.

Priority will be given to supporting both facilitators and supervisors, especially considering they are contending with persistent socioeconomic challenges in both regions. A communal spirit of mutual support and collaboration will be cultivated via group supervision and inter-site conferences. These gatherings will facilitate the exchange of experiences, ideas, and assistance in applying the IPT model.

#### Criteria for discontinuing or modifying allocated interventions {11b}

By agreeing to participate in the trial, participants are giving their consent for intervention, assessments, follow-up, and data collection. However, participants retain the right to withdraw from the study at any point, without the obligation to provide a reason. The study also reserves the right to withdraw participants from treatment under certain circumstances, such as if a designated clinician deems it necessary. Such a decision may arise if there is a notable worsening of symptoms or if the participant develops a new condition that necessitates a different treatment delivered individually. For example, if a participant reports worsening symptoms such as suicidal ideation during their participation in the trial they will be referred to a clinician for review and may be offered additional talking therapy or medication if deemed appropriate.

#### Strategies to improve adherence to interventions {11c}

In ensuring the integrity of this study, we adhere to the fidelity domains outlined by the NIH Behavior Change Consortium [49]. For the study design, our approach is rooted in the interpersonal theory of depression. Both g-IPT and HQ-SC are meticulously standardised in terms of their duration and frequency. We have designed the recruitment and delivery process to avoid any contamination, and any implementation challenges arising will be reviewed in regular weekly meetings that include representatives from the study sites, the training team, and University College London (UCL).

g-IPT facilitators are considered competently trained once they achieve predetermined benchmarks. These include attending at least 80% of the training workshop and supervision sessions, scoring 70% or above in the knowledge test, and reaching a 75% benchmark in g-IPT fidelity on the checklists. The delivery of g-IPT is firmly based on a manual. We are open to potential content adaptations, provided they remain true to the original model. Before launching the RCT, any such amendments will be incorporated into the manual. Our monitoring efforts during the implementation phase include offering consistent feedback to facilitators and selecting a random subset for competence evaluation to ascertain their adherence to the model. Supervisors will oversee these evaluations, with oversight from the master trainers. We aim to evaluate the fidelity of approximately 22% of all sessions through a randomised sampling approach.

Our approach aims to enhance participant engagement from the outset, starting with the pre-group meeting. Our goal is to ensure that every participant not only receives but fully understands the g-IPT skills. We will keep a close eye on session attendance and promptly address any signs that a participant might be at risk of dropping out. The comprehension of participants will be consistently assessed during both onsite and online supervisions, wherein facilitators will elaborate on how they communicated the concepts and how participants responded. Finally, to monitor the enactment of treatment skills, we will observe and bolster participants’ ability to apply g-IPT skills in their day-to-day lives. This will be achieved through regular discussions centred on participants’ practice between sessions, often referred to as “homework”.

#### Relevant concomitant care permitted or prohibited during the trial {11d}

In line with the pragmatic nature of this trial, concomitant care and interventions are permitted as part of the SUMMIT study, based on the judgement of a designated clinician. This encompasses both medications and various forms of therapy. The singular exception is that participants in the HQ-SC care group are prohibited from receiving g-IPT.

#### Provisions for post-trial care {30}

Upon trial conclusion, participants will continue to be monitored by the local research teams for a duration of 1 year from their initial clinical contact. If any concerns arise regarding a participant’s safety during this period, the research teams are equipped and obliged to adhere to the trial’s safeguarding protocol, as well as the established protocol for reporting adverse events.

### Outcomes {12}

#### Primary outcome measure

The primary outcome is the child’s cognitive development at the 52-week (T6) follow-up, measured using the Malawi Developmental Assessment Tool (MDAT) [50]. The MDAT is a widely accepted tool for assessing children’s cognitive development. It has been employed in numerous global health studies focusing on early child development and has demonstrated sensitivity to interventions in various trials.

#### Secondary outcome measures

Secondary outcomes encompass a broad array of metrics:Maternal depression severity, which will be gauged using the Patient Health Questionnaire—depression module (PHQ-9) [32] at multiple time points: baseline (T1), 8 weeks (T2), 13 weeks (T3), 24 weeks (T4), 36 weeks (T5), and 52 weeks (T6).Family circumstances will be evaluated using the family circumstances questionnaire at T1, T3, and T6.The Family Care Indicator (FCI) [51] will be used to measure maternal sensitivity and indicators of family care at T1, T2, T3, T4, T5, and T6.Early childhood development will be assessed using the Caregiver Reported Early Development Index (CREDI) long form [52] at T1, T3, and T5.Anxiety levels will be gauged using the General Anxiety Disorder-7 (GAD-7) [53] at T1, T2, T3, T4, T5, and T6.Sleep patterns of the mother will be assessed using the Sleep Condition Indicator (SCI) [54], while the infant’s sleep will be evaluated using the Brief Infant Sleep Questionnaire—Revised Short form (BISQ) [55]. Both measures will be taken at T1, T2, T3, T4, T5, and T6.The infant’s physical health will be gauged using a dedicated physical health questionnaire, and their nutritional intake will be assessed using the breastfeeding outcome measure at T1, T2, T3, T4, T5, and T6.Social isolation and relationship satisfaction will be evaluated using the Lubben Social Network Scale (LSNS-6) [56] and the Couple Satisfaction Index (CSI-4) [57], respectively, at T1, T3, and T6.Mother’s health and quality of life will be assessed using the EQ-5D-5L [58] and the ICEpop CAPability measure for Adults (ICECAP-A) [59] at T1, T3, T4, and T6.The economic evaluation of the intervention will be determined using the SUMMIT patient cost questionnaire [60] at T3. Additionally, household economic status will be gauged using a Household Economic questionnaire at T1, and household shocks will be assessed based on the Malawi Integrated Household Survey (IHS) [61] at T3.Demographics, including socio-economic status, maternal education, maternal parity, and teen parent status, will be collected using the SUMMIT demographic questionnaire at T1.To further examine the mother’s evolving perceptions or attitudes towards post-natal depression, brief semi-structured qualitative interviews will be conducted at T1, T3, and T6.

### Participant timeline {13}

See Fig. 1.

**Fig. 1 Fig1:**
[figure not shown]
Schedule of enrolment, interventions, and assessments

### Sample size {14}

Power calculations indicate that a sample of 412 participants (*N* = 224 in the g-IPT arm and* N* = 188 in the control arm) offers 90% power to detect a standardised mean difference of 0.40 on the primary outcome, allowing for up to 25% attrition. These calculations are based on a predetermined effect size of 0.4, as informed by the Cuijpers et al. meta-analysis [29], on the primary outcome [62]. They also consider a two-tailed alpha level of 0.05 and account for clustering with an intra-class correlation (ICC) of 0.04 [63] in the treatment arm, further adjusted for an expected attrition rate of 25% [64]. The sample size estimates were derived using the “clsampsi” routine in STATA, with the assumption of a g-IPT group size of 8.

### Recruitment {15}

Four hundred twelve participants will be recruited over a 10-month period in both sites, at approximately 22 participants per month per site. Study teams will aim to recruit 6 participants per week to enable a clinical group to be established.

## Assignment of interventions: allocation

### Sequence generation {16a}

Participants will be randomised to either the control group (high-quality standard care) or the intervention group (high-quality standard care plus g-IPT). The randomisation process will be facilitated through a secure, 24-h accessible web-based platform developed and maintained by NWORTH [65]. Within the platform’s algorithm, the likelihood of a participant being allocated to a specific treatment group is dynamically recalculated based on the participants previously recruited and allocated [65]. This recalibration considers the overall allocation, stratification variables (such as participant age and recruitment site), and within each stratum level (comprising relevant combinations of stratification levels). By constantly recalculating, the algorithm ensures balance is maintained within acceptable limits of the designated allocation ratio, all while ensuring unpredictability in the randomisation process.

### Concealment mechanism {16b}

Local trial coordinators will oversee the randomisation of participants. Once randomised, participants will be informed of their group assignment. However, apart from the local trial coordinators, no other members of the local research teams will be privy to the participants’ group allocation.

### Implementation {16c}

Local trial coordinators will handle the randomisation of participants via a secure, 24-h accessible web-based platform, developed and maintained by NWORTH [65]. In the event of a system malfunction, an emergency randomisation protocol will be activated.

## Assignment of interventions: blinding

### Who will be blinded {17a}

The trial is designed as a single-blind study. All data collectors and principal investigators will remain unaware of the randomisation allocation. The randomisation of participants will be conducted off-site before the onset of the intervention. Given the unequal allocation ratio, the trial statistician will not be blinded throughout the study’s duration. However, the principal statistician (NWORTH co-applicant) who will oversee and approve all analyses will remain blind. Both the central trial coordinator and the local trial coordinators will remain unblinded to effectively oversee the randomisation process, ensuring ethical and appropriate participant allocation with minimal bias.

## Data collection and management

### Plans for assessment and collection of outcomes {18a}

Participants will be invited to complete questionnaires and participate in interviews that explore their personal history, parenting behaviours, health, and interpersonal relationships. Additionally, they will be prompted to answer questions about the health and welfare of their child. Before participants begin the questionnaires, the content will be summarised for them, and they will be reminded of their right to withdraw. This ensures that individuals who might find certain topics challenging or triggering are forewarned and can choose not to participate.

Many of the questionnaires and interview questions have their roots in clinical contexts, ensuring their potential emotional impact on respondents has been thoroughly assessed. The majority of our outcome measures have been validated for use in non-English languages. All questionnaires and interviews are conducted by a local researcher who is fluent in the language spoken by that participant.

The Research Assistants (RAs) tasked with data collection will undergo comprehensive training. This will cover the entirety of the RCT measures pack, as well as guidelines on engaging with participants, conducting interviews, and inputting data. For this particular study, we will employ live data collection methods. Specifically, outcome measures will be input directly into the REDCap database via the REDCap mobile app. REDCap (Research Electronic Data Capture) is a secure, web-based software platform designed to support data capture for research studies, providing (1) an intuitive interface for validated data capture, (2) audit trails for tracking data manipulation and export procedures, (3) automated export procedures for seamless data downloads to common statistical packages, and (4) procedures for data integration and interoperability with external sources [66, 67]. The REDCap database will be hosted by UCL.

### Plans to promote participant retention and complete follow-up {18b}

To enhance participant retention, our local teams will endeavour to gather multiple contact numbers for each participant. For those who do not possess a personal phone, we will collect contact numbers of partners, family members, or even neighbours to maintain an open line of communication throughout the study. In Kenya, our study team will leverage the aid of Community Health Volunteers (CHVs) to assist with participant engagement. These CHVs will prove invaluable in locating participants, especially in instances where the research team faces difficulties in reaching them by phone. As the CHVs maintain affiliations with both health facilities and the communities where the study is to be conducted, they offer a unique and effective bridge. To further promote retention, our local teams will liaise with participants to ensure that follow-up visits are scheduled with the utmost flexibility in mind.

Should a participant miss any or all of the intervention sessions (be it HQ-SC or g-IPT), our research team will still conduct follow-up. In such instances, we will proceed to collect all outcome measures, unless, of course, the participant expresses a desire to withdraw from the study.

### Data management {19}

The study will be conducted in strict accordance with the General Data Protection Regulations (GDPR), Good Clinical Practice (GCP), and relevant Standard Operating Procedures (SoPs). When data are stored locally at individual sites, adherence to the respective University’s SoPs will be ensured. Paramount importance will be given to patient confidentiality. All data will be securely stored on password-protected PCs/laptops, with any paper records safeguarded in locked drawers or filing cabinets within secure premises. Participants’ personal details will be coded and anonymised at the source. Each participant will be assigned a unique study number, which will be consistently utilised in all study-related documentation. The sole personal data retained throughout the study will encompass the consent form and contact details. Apart from the Consent Forms, participants’ names will not feature in any study documents, and no identifiable data will be transmitted outside the host nation. Clinical data will be archived using the participant’s unique study number, ensuring that paper records of the consent form are stored separately from this clinical data.

Quantitative data will be pseudonymised and entered directly into the central REDCap database—a secure, cloud-based platform—using only the participant’s unique study number. Local data collectors will utilise the REDCap app [66, 67], installed on a password-secured tablet, for data collection purposes. They will be thoroughly trained in its usage, complemented by a user manual for reference. The key linking ID codes and personal identifiers will remain securely with the site teams in Kenya and Lebanon, ensuring they remain undisclosed to teams in the UK or USA. All research participants’ personal data will be stored at each research site in password-protected files, exclusively accessible to the research team members.

Participants will be informed of who will have access to their records, along with the specific purposes, as outlined in the information sheet. Only members of the research team will be granted data access. Authorised individuals from the research team and regulatory bodies in both Lebanon and Kenya might review case notes. This access is explicitly specified in the consent form. Training sessions, encompassing GCP and GDPR, are provided to staff at the onset of the trial. In alignment with the GDPR 2018 stipulations, participants will receive detailed explanations regarding the handling of their data and the legal rationale for processing their personal details. The trial will adhere to the Kenya government Data Protection Act 2019, Article 31(c) and (d) of the Kenyan constitution, and the policy of the National Mental Health Programme in Lebanon, ensuring GDPR compliance in Kenya.

### Confidentiality {27}

All data will be processed in alignment with the UK Data Protection Act 1998.

Electronic and paper case report forms (CRFs) will not contain the participant’s name or any personally identifiable information. Instead, the participant’s trial identification number will serve for identification purposes. This procedure will be elucidated in the Patient Information Sheet, and participants’ consent regarding this approach will be obtained.

## Statistical methods

### Statistical methods for primary and secondary outcomes {20a}

All quantitative analyses will be conducted on an intention-to-treat (ITT) basis at the NWORTH Clinical Trials Unit. A comprehensive statistical analysis plan will be drafted and approved by the trial team before data collection concludes and will be open for review by independent committees.

Baseline characteristics will be summarised both overall and by treatment group (intervention and control), as well as by site subgroup. Descriptive statistics for all outcome variables will be generated at every time point.

Categorical variables will be showcased with counts and percentages. Continuous variables will be represented using means, standard deviations, and ranges. For non-normally distributed continuous variables, medians and interquartile ranges will be used.

The CONSORT details will be furnished with data on participant numbers.

The primary analysis will evaluate MDAT scores at 52 weeks post-initial clinical contact. A general linear mixed model will be employed, which accounts for clustering in the intervention arm. This model will adjust for allocation group and study centre. Additional covariates or factors to be integrated into the model will be pre-determined in the SAP. All statistical tests will be two-sided and paired with 95% confidence intervals.

Analyses will be executed in STATA or R, adhering to the ITT principle. The significance level (alpha) will be set at 5% (two-tailed). Linear mixed modelling, taking into account clustering by g-IPT group in the treatment arm, will be used, controlling for stratification factors (site and age group). It will also account for pre-defined covariates and model the longitudinal effects of time, as well as any pertinent time-treatment interactions.

Secondary outcomes will be evaluated using a comparable model suitable for the outcome type and will factor in baseline measures where relevant, in addition to stratification and pre-defined covariates.

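### HQ-SC is delivered in groups, but the power calculation and primary model allow for clustering only by g-IPT group, so both assume without justification that HQ-SC groups add none

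*Protocol article*

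**What the plan says.** Three sections of the protocol article bear on this.

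- **Intervention description {11a}.** HQ-SC "teaches participants how to use a stress management guide over the course of two group sessions", each lasting 60 to 90 minutes. Every participant receives it, and women in the intervention arm go on to g-IPT. HQ-SC is thus the control arm's only trial treatment, although concomitant care is permitted in both arms.
- **Sample size {14}.** With "a sample of 412 participants" ("224 in the g-IPT arm" and "188 in the control arm"), the design "offers 90% power to detect a standardised mean difference of 0.40 on the primary outcome, allowing for up to 25% attrition". The calculations "account for clustering with an intra-class correlation (ICC) of 0.04 [63] in the treatment arm" and assume g-IPT groups of 8.
- **Statistical methods for primary and secondary outcomes {20a}.** "A general linear mixed model will be employed, which accounts for clustering in the intervention arm". The same section later names the g-IPT group as the cluster unit.

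The article does not give the size of HQ-SC groups, an ICC for them, or whether they contain one arm or both. Nor does it say why clustering by HQ-SC group could be neglected.

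**The concern.** The protocol accepts that treatment in groups makes outcomes within a group dependent, and it allows for that in both the sample size and the model. It then applies the principle to one of its two group-delivered treatments. Control participants are handled as independent although they too are treated in groups.

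This is more than a detail deferred to the statistical analysis plan. The article leaves further covariates and factors to that plan, but it fixes the cluster structure itself, and fixes it for one arm.

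The standard error of the primary comparison is at stake. If HQ-SC groups are arm-specific and have any positive ICC, the planned model understates that standard error, which favours declaring superiority. The power would also be somewhat below what the inputs imply.

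**Working it through.** **Inputs from the protocol (Sample size {14})**

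- Two-sided alpha 0.05, standardised mean difference 0.40 (SD = 1).
- 224 and 188 randomised, 25% attrition: 224 × 0.75 = 168 and 188 × 0.75 = 141 completers.
- ICC 0.04 and group size 8 in the g-IPT arm: design effect 1 + 7 × 0.04 = 1.28.

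**Formulas (normal approximation)**

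- SE = √(DE_t/168 + DE_c/141), where DE_t and DE_c are the design effects in the g-IPT and control arms and DE_c = 1 + (m − 1) × ICC_c.
- Power = Φ(0.40/SE − 1.96).
- True alpha if control clustering is ignored = 2Φ(−1.96 × SE_planned/SE_true).

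**Step 1: reproduce the stated figure.** With DE_c = 1, SE = √(1.28/168 + 1/141) = √(0.007619 + 0.007092) = 0.1213. Power = Φ(3.298 − 1.96) = 91.0%. A noncentral t version gives 90.6 to 90.8%. The stated 90% is reproduced.

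**Step 2: arm-specific HQ-SC groups.** ICC_c and m are my assumptions, because the article gives neither.

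| ICC_c | m | DE_c | SE | Power | SE_true/SE_planned | True alpha if ignored |
|---|---|---|---|---|---|---|
| 0.01 | 6 | 1.05 | 0.1227 | 90.3% | 1.012 | 5.3% |
| 0.01 | 8 | 1.07 | 0.1233 | 90.0% | 1.017 | 5.4% |
| 0.02 | 8 | 1.14 | 0.1253 | 89.1% | 1.033 | 5.8% |
| 0.04 | 6 | 1.20 | 0.1270 | 88.3% | 1.047 | 6.1% |
| 0.04 | 8 | 1.28 | 0.1292 | 87.2% | 1.065 | 6.6% |
| 0.04 | 10 | 1.36 | 0.1314 | 86.1% | 1.083 | 7.0% |

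Over groups of 6 to 10 and ICCs of 0.01 to 0.04, power runs from about 86 to 90% and true alpha from about 5.3 to 7.0%.

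**Step 3: let attrition shrink the groups.** The table keeps 8 completers per g-IPT group. Taking 25% off a group of 8 leaves 6. With 6 per group in both arms, DE_t = 1 + 5 × 0.04 = 1.20.

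- No control clustering: SE = 0.1193, power 91.8%.
- ICC_c 0.02 (DE_c = 1.10): power 90.5%.
- ICC_c 0.04 (DE_c = 1.20): SE = 0.1251, power 89.2%, true alpha if ignored 6.2%.

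**Step 4: HQ-SC groups that mix the arms.** Women from both arms then share the group effect, so it largely drops out of the difference between arms. Power stays near 91%. Leaving the term out keeps the shared variance in the residual, so the planned standard error is slightly too large and the test mildly conservative.

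**The case against.** The strongest case on the other side has four parts.

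- **The HQ-SC ICC may be very small.** HQ-SC is two sessions on using a self-help guide. g-IPT is nine sessions, eight of them in groups, of interpersonal work. The outcome is the child's development at 52 weeks, remote from two sessions attended by the mother. This stands: giving HQ-SC the full 0.04 is an upper-end case, and at 0.01 with groups of 8 power is still 90.0%.
- **Composition decides the direction.** The article says that all women receive HQ-SC and that intervention-arm women receive g-IPT afterwards, which is compatible with mixed groups. Its statement that delivery is designed to avoid contamination could point the other way. This stands too: the direction cannot be settled from the document.
- **The 87.2% assumes that groups lose no members.** Step 3 confirms that the loss is smaller once they do, though alpha still reaches 6.2% at the upper-end ICC.
- **The analysis plan may add a term.** It may, but the protocol's wording fixes clustering to the intervention arm, so a change there would be a departure needing explanation.

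A reader might infer that the 90% power and the standard error are simply wrong, or that they must be wrong however the groups were formed. The document does not support that: the 90% reproduces, and with an HQ-SC ICC near zero neither arrangement causes a material error. A reader might also infer that controls shared a leader as g-IPT women did. The article does not say who led HQ-SC sessions.

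**Conclusion.** The inconsistency is real: both treatments are given in groups, but clustering is recognised for one only, and nothing is offered to justify that. The stated power and the planned standard error are conditional on zero clustering by HQ-SC group.

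The consequence is modest and conditional. Against the stated 90%, arm-specific groups cost about 0 to 4 percentage points of power, and true alpha is about 0.3 to 2.0 points above 5% if the planned model is kept. Mixed groups bring no meaningful loss. These ranges rest on an assumed ICC of 0.01 to 0.04 and groups of 6 to 10. The alpha effect matters more than the power effect, because recruitment has closed and the model can still be corrected. I rate this as a moderate point to settle before analysis, not as a fatal flaw.

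**What to change.** 1. Take each woman's HQ-SC group from attendance records, and state how the groups were formed and whether they were arm-specific or mixed.
2. Before analysis, amend the primary model to add an HQ-SC group random intercept alongside the g-IPT group effect. If groups were arm-specific, place it in the control arm and consider whether the g-IPT arm had a separate HQ-SC grouping that also needs a term. If groups were mixed, fit it across both arms.
3. Restate power as a range over control-arm ICCs, with the ICC and HQ-SC group size labelled as assumptions. For arm-specific groups the table above gives about 86 to 90%. For mixed groups power stays near 91%.

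The cost is a group identifier in the dataset, slightly more analysis work and a slightly less favourable power statement. No extra participants are needed. Settling this beforehand also avoids choosing the error structure of the primary result after seeing the data.
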